## 7 METHODS

### 7.1 Method overview

This is a prospective multicenter randomized controlled trial. Screening for study subjects takes place among women with threatening premature birth in the antenatal and labor ward, with randomization taking place antenatally. The study population is 150 infants (75 infants in control and in intervention) born between gestational age 28+0 and 32+6 weeks at Karolinska University Hospital labour wards in Danderyd and Huddinge in Stockholm and at Stavanger Universityhospital in Norway. The intervention is skin-to-skin contact with either parent or with a surrogate chosen by them, the SSC should be uninterrupted during the first six hours of life, and as much as possible in the first 72 hours. Data will be collected during this time, and then during the period of admission, and continued until the infant reaches 24 months corrected age (described further below). Certain selected outcomes will be studied in subsamples of the 150 subjects, and for practical reasons some at only one site. Some families studied may later be transferred elsewhere in the country, data for these will continue to be collected as far as possible. There may also be certain exclusions due to language and interpreter problems that may influence data. Discussion on sample sizes for subsamples is ongoing.

## 7.2 Assessment and procedures

Note that in the following section the corrected age is used, that is to say time from the expected date of full-term birth, and not the chronological age calculated from the actual premature date of birth.

### Antenatal:

- Information about the study.
- Gathering of consent.
- Gathering of background information (parent's education, information about family, address, smoking, earlier illnesses and pregnancy related problems from the mother, antenatal corticosteroids).
- Randomization when birth is inevitable and imminent, at latest one hour before birth.

### As soon as possible after birth:

- Cord blood and buccal swab is taken from the infant for epigenetic testing.
- Fecal sample and skin swab taken from the infant for analysis of microbiota
- Maternal samples from rectum, vagina and skin for microbiota analysis.
- Father or partner swabbed for microbiota analysis.
- HRV

### From birth through the first six hours of life:

- Intervention or conventional care. Intervention is continuous skin-to-skin contact.
- Physiological parameters collected by direct observation of infant and by pulse oximetry.
- Axillary temperature measured continuously and recorded every hour for infant, and for SSC group also on the parent.
- At any stage during the first 6 hours, when normal routine whole blood collection is undertaken, an additional sample is taken for epigenetic analysis.

### At 6 hours of age

- Buccal swab is taken from the infant for epigenetic analysis.

### From 6-72 hours of age

- Intervention continued, or conventional care recorded. The intervention is intermittent SSC and striving to achieve continuous. Time in SSC and time in any other place is carefully recorded.
- Clinical information is collected from observations, or from case record review.
- Information on first feeding, on type of feeds given, and first passage of meconium is recorded.

### At 48-72 hours (in conjunction with the PKU-test):

- Buccal swab and whole blood sample for epigenetic analysis.
- Fecal sample, and nasal and skin swab taken for microbiota analysis.
- HRV

### Age 4-10 days:

- EEG

### Age 7 days:

- Breastfeeding questionnaire BSES completed.
- Questionnaires EPDS och STAI completed.

Each week during admission:

- Nutritional status including questionnaires IBS and IBFAT completed.

At discharge:

- Information on need for respiratory support collected from hospital case record.
- Information on infections collected from hospital case record.
- Information on growth collected from hospital case record.
- Skin-to-skin contact time and care in other place during hospital stay collected.
- Lowest weight, current weight and weight gain per day collected from hospital case record.
- Nutritional status including questionnaires IBS och IBFAT complete for hospital stay.
- HRV
- Parents are interviewed about their experience of care, including benefits and challenges with care in skin-to-skin contact.
- Salivary cortisol measured on mother and on infant in the morning and the evening, as well as before and after a nappy change.

At follow-up visit when reached term age:

- HRV
- Psychomotor developmental assessment according to standard hospital follow-up program.
- Observation according to APIB.
- The questionnaires EPDS, STAI and SPSQ completed.
- The questionnaires IBS and IBFAT completed.

At another visit when term age:

- EEG
- Observation according to APIB (if not done at the routine visit)

At another visit when term age:

- Structural maturation of brain according to MRI.

At follow-up visit 3-4 months corrected age:

- Psychomotor developmental assessment according to standard hospital follow-up programme.
- Buccal swab and whole blood collected for epigenetic analysis.
- Fecal sample and skin swab taken from the child for microbiota analysis.
- Questionnaires IBS, BSES and IBFAT completed.
- Questionnaires EPDS, STAI and SPSQ completed.
- Questionnaires ASQ and IBQ completed.

At another visit 3-4 months corrected age:

- Assessment of attachment and interaction between parent and infant done through the "Still Face"-test.
- Filming and scoring of Parent-Child Early Relational Assessment Scale (PCERA).
- Salivary cortisol is measured morning and evening as well as before and after the "Still Face"-test.
- HRV measured before, during and after the "Still Face"-test.

At another visit 3-4 months corrected age:

- Functional MRI of brain of mother.

At routine follow-up visit 12 months corrected age:

- Psychomotor developmental assessment according to standard hospital follow-up program.
- Filming and scoring of Parent-Child Early Relational Assessment Scale (PCERA).
- Fecal sample and skin swab taken from the child for microbiota analysis.
- Salivary cortisol measured on infant and mother.
- Questionnaire IBS completed.
- Questionnaires ASQ and IBQ completed.
- Questionnaires EPDS, STAI and SPSQ completed.

At follow-up visit when 24 months corrected age:

- Psychomotor developmental assessment according to standard hospital follow-up program.
- Filming and scoring of Parent-Child Early Relational Assessment Scale (PCERA).
- MCHAT completed.
- Buccal swab and whole blood collected for epigenetic analysis.
- Fecal sample and skin swab taken from the child for microbiota analysis.

At another visit when 24 months corrected age:

- Developmental assessment according to the Bayley Scales of Infant and Toddler Development

### **7.3 Flow chart**

Attached, see Appendix 2

### **7.4 Trial completion**

The study will be complete when the last enrolled subject comes for follow-up visit at 24 months corrected age, approximately 2 years and 3 months after last enrollment.

## **8 TRIAL SUBJECTS**

### **8.1 Inclusion criteria**

- Birth at gestational age between 28+0 and 32+6 weeks.
- Born in labor ward at study site.
- Consent from prospective parents, with interpreter if required.
- Parent or surrogate available to commence skin-to-skin contact in the first hour of life.

### **8.2 Exclusion criteria**

- Born outside hospital
- Triplets or higher multiples
- Known congenital malformation requiring surgical management.
- Known congenital infection.
- Any other circumstance precluding subject from enrollment according to responsible clinician.

### **8.3 Criteria for interruption and cessation**

The intervention will sometimes not be able to be initiated immediately and will at times require to be temporarily halted for events and procedures that cannot be done safely in SSC. This does not imply withdrawal from the study, as such situations are expected. Prospective parents will have consented to study participation with information about the importance of adhering to allocated place of care in the first six hours of life. Clinical staff will support such adherence. If parents demand otherwise, this may be accepted after individual assessment by the clinically responsible neonatologist as to safety of infant. Actual time in allocated place of care, as well as time in other place of care will be documented. Criteria for temporary interruption of SSC, with intention to continue straight after, will be:

- If the infant requires intubation
- If the infant requires umbilical catheters
- If infant despite adequate measures has hypothermia
- If infant despite support has repeated severe apnoea and bradycardia
- If infant requires any other intervention and this cannot be done safely in SSC, as assessed by ward staff and responsible neonatologist.

Should the parents of any study subject wish to withdraw from the study this will be accepted. Data collected up to that point will be analyzed unless the parents expressly wish otherwise. Clinical staff may also in consultation with research staff choose to terminate a subject's participation under particular circumstances.

### **8.4 Recruitment register**

All women admitted for threatening premature labor will be logged on a screening list and allocated a screening number. All reasons for non-inclusion in the study will be documented on this list.

## ***TREATMENT***

### **8.5 Description of treatment**

Not applicable

### **8.6 Determination of allocation**

Randomization will be done by electronic means, close to the actual birth time but at earliest 6 hours before birth and latest one hour after birth.

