## 6 ENDPOINTS

### 6.1 Primary endpoints

Cardiorespiratory stability is measured with the SCRIP score (Stability of the CardioRespiratory system In the Preterm), a scale that summates the respiratory (respiratory rate, oxygen saturation, need for respiratory support) and circulatory (pulse) variables in the infant (7). Observations are made during a five-minute period every 15 or 30 minutes during the first six hours, according to prepared template. For each five-minute period the recorded parameters are used to calculate a summary score of physiological stability.

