# 9 ASSESSMENT OF SAFETY AND EFFECTIVENESS

## 9.1 Assessment of clinical effectiveness

SCRIP-score: Respiratory rate, heart rate and oxygen saturation are measured and scored in a table, need for respiratory support is part of the table. The average of total scores is analyzed.

HRV: Heart rate variability is measured for an appropriate interval, possibly using the "Faros 360" and analyzed according to Porges method by the Nurture Science Programme, Columbia University, NY. Average and median values are analyzed.

Respiration: Need for surfactant, number of days in ventilator, number of days in CPAP, number of days requiring supplemental oxygen collected from hospital case record. Proportions and median values will be analyzed.

Temperature: Axillary temperatures will be recorded. Average and median values are analyzed.

Infection: Proportion of infants experiencing sepsis during admission collected from hospital case record, as well as days receiving antibiotics. Average and median values are analyzed.

Breastfeeding and nutrition: Age at first feed, age at first passage of meconium, time to full enteral nutrition, lowest weight, time to removal of feeding tube, time to regained birth weight, weight gain in grams per day during hospital stay, weight at discharge and at term age is collected from the hospital case record. Breastfeeding status is determined from Index of Breastfeeding Status, Breastfeeding Self-Efficacy Questionnaire and Infant Breastfeeding Assessment Tool (IBFAT). A PhD student will be responsible for extracting data from case record (Take Care and Clinisoft). A research nurse will distribute questionnaires and parents will complete them during admission or at home prior to follow-up visits. Proportions are analyzed.

Epigenetics: Whole genome analysis as well as locus specific methylation of stress related genes for Oxytocin receptor (OXTR), glucocorticoid receptor (NR3C1), Arginine-vasopressin receptor (AVP), Proopiomelanocortin (POMC), Glutamate decarboxylase-1 (GAD1), Glutamate receptor (GRM1), Brain-Derived Neurotrophic Factor- (BDNF), serotonin transporter (SLC6A4 och SERT), serotonin receptor (5H2A) och serotonin degradation enzyme

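### Section 8.6 allows randomisation up to one hour after birth, while 7.1 and 7.2 place it before birth, and nothing reconciles the two rules

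*Protocol*

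**What the plan says.** Three places in the protocol fix the time of randomisation.

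- Section 7.1 describes the design "with randomization taking place antenatally".
- Section 7.2, in the antenatal list, has "Randomization when birth is inevitable and imminent, at latest one hour before birth".
- Section 8.6, the section on allocation, has it done electronically, "close to the actual birth time but at earliest 6 hours before birth and latest one hour after birth".

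Other provisions determine what the conflict means in practice.

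- Section 6.1 defines the SCRIP schedule: "Observations are made during a five-minute period every 15 or 30 minutes during the first six hours, according to prepared template". Section 7.2 lists the physiological data under "From birth through the first six hours of life". Section 9.1 adds: "The average of total scores is analyzed".
- Section 8.2 ends with an open exclusion that has no time limit: "Any other circumstance precluding subject from enrollment according to responsible clinician".
- Section 8.7 says that allocation cannot be blinded. Section 11.2 limits the intention-to-treat set to randomised subjects who met the inclusion criteria and no exclusion criterion.

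**The concern.** A site cannot follow all three sections. An infant randomised 30 minutes after birth complies with 8.6 and breaches 7.1 and 7.2. The wording of 8.6 reads coherently as a window around birth, so it cannot be dismissed as a slip, and staff would naturally look there for the rule.

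Two consequences follow if 8.6 is applied. First, after birth the staff have seen part of the transition that the primary outcome measures, and the discretionary exclusion can be used with that knowledge. Second, scores collected between birth and allocation belong to neither arm, yet they would enter a six-hour average and pull the arms together. Section 11.3 already expects a smaller difference than the earlier trials found, so avoidable dilution matters.

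There is also a practical fault in 8.6. Its earliest limit is counted back from a birth time that nobody knows at the moment of randomisation, so compliance cannot be checked then.

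**Working it through.** The protocol states no figure that depends on randomisation time, so there is none to reproduce. The check compares the limits and then does arithmetic on the outcome window.

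**1. Gap between the limits.** Counting from birth, 7.2 gives −1 hour as the latest time and 8.6 gives +1 hour. The difference is 1 − (−1) = 2 hours. Section 7.1 (antenatal) agrees with 7.2 but does not itself state the one-hour margin. No section says which rule prevails, and none starts the outcome window at randomisation.

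**2. Largest unallocated share for one infant.** With the window taken as six hours from birth (6.1 with 7.2), randomisation at 60 minutes leaves 60/360 = 16.7% of the window before allocation:

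- at 15-minute spacing, 4 of 24 observations
- at 30-minute spacing, 2 of 12 observations

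Under an antenatal rule the share is zero.

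**3. Dilution of a six-hour average.** Assumptions: equally weighted scores, no arm difference before allocation, a constant difference afterwards, and unchanged variance. Let h be the delay from birth to allocation in hours, averaged over all infants, with antenatal randomisation counted as zero.

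- Retained effect: r = 1 − h/6
- Factor on the number of infants for the same power: 1/r²
- Power, starting from a nominal 90%, two-sided 0.05: Φ(r × (1.960 + 1.282) − 1.960)

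| h (hours) | r | 1/r² | Power |
|---|---|---|---|
| 0 | 100% | 1.00 | 90.0% |
| 0.25 | 95.8% | 1.09 | 87.4% |
| 0.5 | 91.7% | 1.19 | 84.4% |
| 1.0 | 83.3% | 1.44 | 77.1% |

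The last row requires every infant to be randomised at exactly 60 minutes, so it is an upper bound. For a milder case, suppose that 25% of infants are randomised after birth at a mean of 30 minutes. Then h = 0.25 × 0.5 = 0.125, r = 97.9% and 1/r² is about 1.04.

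**4. Dependence on the endpoint.** Section 9.1 analyses the average of total scores, to which step 3 applies. Section 11.3 sizes the trial on the proportion with the maximum score at 6 hours of age. The 1/6 calculation does not apply directly to that summary, which is less affected. The nominal 90% in the table is only a starting point; it is not the trial's calculated power for the averaged score.

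**The case against.** The strongest reply is that the contradiction is real but its harm is limited. Most of that reply stands.

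- **Bias between arms.** A reader might infer that seeing the infant first biases the comparison. The documents do not support this. Randomisation is electronic and nothing shows a failure of concealment. If the arm is unknown until the call, postnatal selection changes who is enrolled, not how the arms compare. The discretionary exclusion exists under either timing, and 8.4 requires reasons for non-inclusion to be logged. The log documents selection but does not prevent it.
- **Start of scoring.** Section 6.1 does not give the time of the first score. Scoring from birth is the natural reading with 7.2, but it is an inference.
- **Start of skin-to-skin contact.** A reader might infer that randomisation at 60 minutes breaches the inclusion criterion. That criterion is "Parent or surrogate available to commence skin-to-skin contact in the first hour of life", which concerns availability. Sections 8.3 and 14.2 already expect some delayed starts.
- **Size.** A reader might take 1.44 as the expected inflation. It is the extreme case, the number randomised after birth is not given, and dilution of this kind pulls towards no difference.
- **Cost of an antenatal rule.** Gestational age at birth and birth at a study site are confirmed only at birth, so some infants randomised beforehand may prove ineligible. This is a genuine trade-off. It bears on which rule to choose, and does not excuse stating both.

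**Conclusion.** The protocol contradicts itself on a core design element, and the passages must be reconciled. That conclusion needs no assumption.

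The consequences are conditional. Under 8.6, enrolment can depend on the infant's early state; this affects the population enrolled and cannot be sized from the document. For the averaged SCRIP score counted from birth, up to 16.7% of an infant's window precedes allocation. Average delays of 0.25 to 1 hour leave 96% to 83% of the effect, given no arm difference before allocation. It would go too far to conclude that the arm comparison is biased, or that the sites have in fact applied different rules. The document shows neither.

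**What to change.** 1. State one limit in 7.1, 7.2 and 8.6: randomisation before birth, as 7.1 and 7.2 already say.
2. Require eligibility, including the discretionary exclusion in 8.2, to be recorded in the electronic system before the arm is shown. This matters under antenatal randomisation too, because 11.2 removes subjects with an exclusion criterion from the analysis set and an untimed one could otherwise be applied with the arm known.
3. Replace the six-hour earliest limit in 8.6 with a criterion that can be verified at the time. Section 7.2 already has one: birth judged inevitable and imminent. Keep infants born later than expected in their arm, and say how those who prove ineligible under 8.1 at birth are handled.
4. Section 4.2 describes the trial as already running in Stavanger and Huddinge, so an amendment cannot change past allocations. Record and report randomisation time relative to birth for every infant. Add a sensitivity analysis of the primary outcome that excludes SCRIP scores from the first hour in both arms, or excludes infants randomised after birth.

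Starting the six-hour window at randomisation is not a good substitute, because infants would then be scored at different postnatal ages.

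The cost is a protocol amendment, a site instruction and one extra recorded time. Some precipitous births will not be enrolled, and some infants randomised antenatally may prove ineligible at birth.

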### **8.7 Blinding and breaking code**

The intervention is such that blinding of allocation is not possible.

## 8.8 Concomitant study interventions and medications

Participation in other intervention studies will not be permitted unless these are observational studies. There are no pharmacological contraindications to participation obs check participation?

## 8.9 Compliance

Information about the study is given to the parents antenatally as part of obtaining informed consent. At that time the importance of maintaining place of care according to the randomization will be emphasized. Compliance to study protocol and achieving the maximum dose of intervention and control care will also require training and instructions to all ward staff. All staff involved in care will receive practical training on all aspects of the intervention, and recommendations on where what procedures can be done. Time in skin-to-skin, time sent elsewhere and reasons for any transfers will be documented.

## 8.10 Treatment after the study

After the last data collection at 24 months corrected age there will be no further follow-up of study subjects or their parents.

# 9 ASSESSMENT OF SAFETY AND EFFECTIVENESS

## 9.1 Assessment of clinical effectiveness

SCRIP-score: Respiratory rate, heart rate and oxygen saturation are measured and scored in a table, need for respiratory support is part of the table. The average of total scores is analyzed.

HRV: Heart rate variability is measured for an appropriate interval, possibly using the "Faros 360" and analyzed according to Porges method by the Nurture Science Programme, Columbia University, NY. Average and median values are analyzed.

Respiration: Need for surfactant, number of days in ventilator, number of days in CPAP, number of days requiring supplemental oxygen collected from hospital case record. Proportions and median values will be analyzed.

Temperature: Axillary temperatures will be recorded. Average and median values are analyzed.

Infection: Proportion of infants experiencing sepsis during admission collected from hospital case record, as well as days receiving antibiotics. Average and median values are analyzed.

Breastfeeding and nutrition: Age at first feed, age at first passage of meconium, time to full enteral nutrition, lowest weight, time to removal of feeding tube, time to regained birth weight, weight gain in grams per day during hospital stay, weight at discharge and at term age is collected from the hospital case record. Breastfeeding status is determined from Index of Breastfeeding Status, Breastfeeding Self-Efficacy Questionnaire and Infant Breastfeeding Assessment Tool (IBFAT). A PhD student will be responsible for extracting data from case record (Take Care and Clinisoft). A research nurse will distribute questionnaires and parents will complete them during admission or at home prior to follow-up visits. Proportions are analyzed.

Epigenetics: Whole genome analysis as well as locus specific methylation of stress related genes for Oxytocin receptor (OXTR), glucocorticoid receptor (NR3C1), Arginine-vasopressin receptor (AVP), Proopiomelanocortin (POMC), Glutamate decarboxylase-1 (GAD1), Glutamate receptor (GRM1), Brain-Derived Neurotrophic Factor- (BDNF), serotonin transporter (SLC6A4 och SERT), serotonin receptor (5H2A) och serotonin degradation enzyme

(MAOA) i cord blood postpartum, in buccal swabs postpartum. Midwife or nurse in labour ward collect cord blood concomitant with routine collection. Neonatal nurse collects blood samples at the same time as required clinically, as well as buccal swab during hospital stay or at follow-up visit. Samples are transported to the Unit for "Medicinsk Epigenetik, Centrum för Molekylärmedicin", KI. Analysis is undertaken by responsible researcher.

Microbiota: Infant microbiome colonization is identified with DNA analysis from fecal samples and skin swabs, and compared to that of their parents. Samples from infant are collected by ward nurse. Tests from parents are collected by nurse, or by the parents themselves. Samples are sent to the Center for Translational Microbiome Research (Molekylär- och Tumörbiologiskt Centrum; MTC).

Brain function maturation: EEG is measured with 8 leads using existing apparatus in clinical use. The results will be interpreted by the Nurture Science Programme, Columbia University, NY.

Structural maturation of brain: MR brain will be done on a subsample at term age. Results will be interpreted by radiologists.

Attachment: attachment will be assessed by psychologist on films made during the "Still Face-test" as well as the Parent-Child Early Relational Assessment Scale (PCERA). Filming is done by research staff. A psychologist or other appropriately trained staff at Linköping University or Karolinska Institutet will interpret the films.

Brain function: Functional magnetic resonance imaging (fMRI) will examine activation patterns in specific areas on mother's brain while she looks at pictures of her own and other infants in different moods. Parents will be invited to radiology department and the examination conducted by radiologists who will assess whether there are any structural differences, with the hypothesis that functional and structural connectivity in parenting behavior specific areas (e.g. prefrontal cortex and amygdala) are related to time in SSC.

Parental mental health: Experience of care will be assessed in interviews at discharge. Questionnaires Edinburgh Postnatal Depression Scale (EPDS), The Spielberg State-Trait Anxiety Inventory (STAI) and the Swedish Parenthood Stress Questionnaire (SPSQ) are administered. A research nurse distributes the questionnaires and parents complete them during hospital stay or at home before follow-up visit. Proportions are analyzed.

Stress reactivity: Salivary cortisol levels measured in infant and mother. A clinical nurse takes the saliva sample during hospital stay or at follow-up. Samples not taken at visit (planned morning and night samples) are collected by parents and sent. Samples are collected at CMM and will later be sent to the University Hospital in Linköping for analysis by immunoassay. Co-variability in mother-infant tests will be analyzed.

Infant psychomotor development: Assessed by APIB; further as described in hospital case record at follow-up visit according to Infant Behaviour Questionnaire (IBQ) and Ages and Stages Questionnaire (ASQ), also developmental assessment according to Bayley Scales of Infant and Toddler Development 3rd Edition and Modified Checklist for Autism in Toddlers (MCHAT). PhD student will collect data from hospital case record. Parents complete questionnaires before follow-up visits. A psychologist will document developmental assessment in case record, a PhD student will collect this. Averages and proportions are analyzed.

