### 6.2 Secondary endpoints

The time points below are the *corrected age* of the infant, calculated from expected date of full-term birth (not the chronological age calculated from actual date of premature birth). For some secondary outcomes only a subsample of infants will be studied.

Respiratory function: Need for surfactant, number of days in ventilator, number of days in CPAP, number of days requiring oxygen.

Heart rate variability: Postpartum, after 48-72 hours, at discharge and at 3-4 months.

Thermal regulation: Axillary temperature is measured continuously, alternatively every hour on infant, and if in SSC also on parent.

Infections: Proportion of infants that experience sepsis during admission in the neonatal ward according to case record, and total number of days treated with antibiotics.

Breastfeeding, nutrition, and growth: Age at first feed, age at first passage of meconium, time to full enteral feeding, time to weaning from feeding tube, lowest weight, time to return to birth weight, weight gain in grams per day during admission, and weight at discharge as well as term age as per case record. Nutrition and breastfeeding status will be completed weekly according to the Index of Breastfeeding Status (IBS) questionnaire during hospital stay, at discharge, at term age, at 3-4 months of age and at 12 months. The Breastfeeding Self-Efficacy Questionnaire (BSES) will be completed at 7 days, 3-4 months, and the Infant Breastfeeding Assessment Tool (IBFAT) each week during admission, at discharge, at term age and at 3-4 months.

Epigenetics: Whole genome analysis as well as locus specific methylation of stress related genes for Oxytocin receptor (OXTR), glucocorticoid receptor (NR3C1), Arginine-vasopressin receptor (AVP), Proopiomelanocortin (POMC), Glutamate decarboxylase-1 (GAD1), Glutamate receptor (GRM1), Brain-Derived Neurotrophic Factor- (BDNF), serotonin transporter (SLC6A4 och SERT), serotonin receptor (5H2A) och serotonin degradation enzyme (MAOA) in cord blood postpartum, in buccal swabs postpartum and at 6 hours, whole blood from opportune time during first 6 hours, whole blood and buccal swabs at 48-72 hours, at 3-4 months and at 24 months of age.

Microbiota: Infant colonization by microbiome (bacteria) is identified by DNA analysis from fecal samples at 0-6 hours, 72 hours, 3-4 months, 12 och 24 months, and compared to the parents. Vaginal, rectal, and skin samples from mother and partner are collected at 0-6 hours.

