### 14.2 Ethical conduct of the study

The study will be conducted according to this protocol, and according to GCP, and according to the declaration of Helsinki. All investigators and research staff will have GCP training.

Risk of hypothermia:

A pilot study (10) suggested that infants of this gestational age may run the risk of hypothermia when cared for in SSC. To ensure that infants allocated to intervention stay warm they will be carefully dried before they are placed on parent's chest, and then covered with warmed textiles. The very smallest and those requiring longer stabilization may start on the resuscitaire where adequate warmth is ensured while ventilation or CPAP is initiated. Should any infant in SSC become hypothermic despite the described measures, it will be placed in a warm incubator and then return to SSC only when temperature is normal.

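### Temperature, a named safety parameter, is analysed only as average and median, which dilute short, treated episodes of hypothermia; no between-arm comparison of hypothermia is named

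*Protocol*

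**What the plan says.** Section 9.1 fixes the temperature summary: "Temperature: Axillary temperatures will be recorded. Average and median values are analyzed". Section 6.2 describes only how temperature is measured: "Axillary temperature is measured continuously, alternatively every hour on infant, and if in SSC also on parent". Section 7.2 adds, for the first six hours, "Axillary temperature measured continuously and recorded every hour for infant".

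Section 1 lists thermal control among the safety parameters, and section 9.2 limits the clinical safety assessment to respiration, temperature and infection. Section 14.2 explains why temperature matters here: "A pilot study (10) suggested that infants of this gestational age may run the risk of hypothermia when cared for in SSC".

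The handling of a cold infant is also set out. Section 8.3 lists, among the reasons for a temporary break in SSC, "If infant despite adequate measures has hypothermia", and says that such breaks are not withdrawal. Section 14.2 says of an infant who becomes hypothermic in SSC that "it will be placed in a warm incubator and then return to SSC only when temperature is normal". Section 11.2 keeps the entire sample for safety measures. It also has continuous variables described with, among other statistics, their minimum and maximum.

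**The concern.** The harm that the pilot points to is an episode: some infants become cold for a time. The protocol's rule ends that episode by rewarming in an incubator, and the readings taken there still count in the SSC arm. A mean over all readings spreads a short fall across the normal ones. A median can pass over it altogether.

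Section 4.3 names the safety of the method as part of the aim, and section 14.3 says that the findings should inform whether SSC is extended to smaller and sicker infants. If the arms are compared only on average and median, a real excess of hypothermic infants in the SSC arm could go undetected in that comparison. The result could then be read as evidence of thermal safety.

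The protocol treats the other two safety parameters differently. For infection it names the proportion with sepsis, and for respiration it analyses proportions as well as medians. For weight it takes the lowest value. Temperature gets neither a proportion nor a lowest value.

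**Working it through.** The protocol gives no effect size, power or hypothermia rate for temperature, so there is no stated figure to reproduce. The check asks how much of a short, treated episode each summary retains.

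**From the protocol.** 75 infants per arm (section 7.1). Hourly recording over the first six hours (section 7.2), taken as 7 readings at 0 to 6 h. Two-sided 5% test, borrowed from section 11.3.

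**Assumed, not in the documents.** Infant mean temperature 37 C, SD between infants 0.3 C, SD within infant 0.2 C. Infants with an episode: 5% of controls and 20% of SSC infants. Each episode lowers 1 or 2 consecutive readings by 1.0 or 1.5 C.

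**Shift in the arm mean.** Difference = (0.20 − 0.05) × fall × (low readings / 7).
- Smallest case: 0.15 × 1.0 × 1/7 = 0.021 C.
- Largest case: 0.15 × 1.5 × 2/7 = 0.064 C.

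**Precision of the mean.** SD of an infant's mean = √(0.3² + 0.2²/7) = 0.309 C. Standard error of the difference = 0.309 × √(2/75) = 0.0505 C. The shift is therefore 0.021/0.0505 = 0.42 to 0.064/0.0505 = 1.27 standard errors, well short of the 2.80 needed for 80% power.

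**The median.** With 7 readings the median is the fourth in rank. If only 1 or 2 readings are low, it is still one of the unaffected readings, so it hardly moves.

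**Simulated power** (4,000 trials per row). Mean, median and lowest reading per infant are compared by t-test, and proportions by z-test. The cuts are devices for the simulation, not clinical limits.

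| Fall, low readings | Mean | Median | Lowest | Any <36.0 | Any <36.25 | Any <36.5 |
|---|---|---|---|---|---|---|
| 1.0 C, 1 | 7% | 5% | 39% | 42% | 42% | 27% |
| 1.5 C, 1 | 9% | 5% | 57% | 72% | 58% | 31% |
| 1.0 C, 2 | 13% | 6% | 44% | 52% | 50% | 29% |
| 1.5 C, 2 | 21% | 6% | 62% | 76% | 59% | 31% |

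Repeat runs differ by a point or two: 6% to 21% for the mean, and 26% at the bottom and 74% to 76% at the top for the proportion. If every episode were identified without error, the proportion would have about 82% power. At the 36.5 C cut about 28% of controls are flagged, which is why power falls there.

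**Other inputs.** With mean 36.9 C, SDs 0.25 and 0.15 C, low readings near 35.6 C and a 36.0 C cut, episodes stand clear of normal readings:
- 5% v 20%, 1 to 2 low readings: mean 10% to 23%, median 5% to 7%, lowest 63% to 68%, proportion 80% to 81%.
- 5% v 25%, 1 to 3 low readings: the mean differs by 0.04 to 0.11 C with power 16% to 59%; median 5% to 11%, lowest 84% to 86%, proportion 94% to 96%.

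**Where the mean does well.** A general shift of the whole SSC arm by 2.80 × 0.0505 = 0.14 C would be detected with 80% power.

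**The case against.** Section 9.1 concerns effectiveness, while safety is handled in 9.2 and section 10. The adverse event definition in 10.1.1 is broad enough to cover hypothermia, 10.5 documents every adverse event, and 8.9 records the reasons for transfers. The Data Safety Monitoring Board (DSMB) receives outcome reports meant to reveal large differences between the groups. The wording in 9.1 is also loose: the infection line gives a proportion and then repeats the same average-and-median sentence. A separate SAP may derive more from the recorded temperatures.

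Much of this stands as description, but it does not close the gap. None of these sections names a comparison of hypothermia between arms. The examples of adverse events in 10.3 leave hypothermia out, 9.4 says that safety margins do not apply to any outcome, and transfer reasons are kept under compliance. The point rests on the summary that 9.1 does name, not on missing detail.

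Four stronger readings are tempting, and the documents do not support them.
- A reader might infer that hypothermia is the one harm the protocol foresees. Section 4.2 calls obstructive apnoea the main risk and also mentions poorer observation. Hypothermia is the harm for which pilot evidence is cited.
- A reader might infer that the harm is averaged away and that a clear excess would surface nowhere. The mean is diluted, not nulled, and the recorded events, transfers and minimum could show some of it.
- A reader might infer that a proportion would have about 82% power. That needs perfect identification of episodes; with a temperature cut it can be much lower.
- A reader might want moves to an incubator compared between arms. Controls are already cared for in incubators, so that comparison is lopsided by construction.

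**Conclusion.** The point holds in limited form. The summaries named in 9.1 suit a general shift in temperature but not the short, treated episodes that 14.2 anticipates, and no between-arm comparison of hypothermia is named. Under the first set of assumptions the mean has about 6% to 21% power and the median 5% to 6%. The lowest reading per infant has 39% to 62%, and the proportion about 26% to 76% depending on the cut.

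These figures depend on assumed rates, depths and durations. With longer episodes and a larger excess the mean reaches 59%. The ordering is stable for short episodes: in every case examined, the lowest reading and the proportion did better than the mean, and the median did worst. The primary outcome is not affected. This is a weakness in one safety measure that can be put right with data already collected.

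**What to change.** In sections 9.1 and 6.2, add two comparisons between arms as randomised:
- the lowest axillary temperature per infant in the first six hours, taken from the hourly recorded values in both arms, since a minimum depends on how many readings feed it;
- the proportion of infants with hypothermia, using the definition the sponsor already applies under 8.3 and 14.2. The protocol does not give that definition, so the sponsor should state it; none is proposed here.

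Include both in the DSMB reports. Report interruptions of SSC for hypothermia descriptively, within the SSC arm only. Keep average and median as measures of overall thermal control.

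The cost is protocol wording, a little extra analysis and one or two more secondary safety comparisons. Hourly temperatures and transfer reasons are already recorded, and no clinical rule changes.
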